## Abstract

**Background:**

Reducing sugar-sweetened beverage (SSB) intake is an important dietary target among underserved children at high risk for obesity and associated morbidities. Community-based approaches to reduce SSB intake are needed. The use of narrative-based approaches (presenting messages within the context of a story) can facilitate connection with target health messages and empower children as behavior change agents within their families. The H_2_GO! program is a community-based behavioral intervention that integrates narrative-based strategies to reduce SSB consumption and promote water intake among school-age youth and parents.

**Methods:**

Guided by the Social Cognitive Theory and the Social Ecological Model, the H_2_GO! intervention consists of 6 weekly sessions that target beverage knowledge, attitudes, and behaviors through youth-produced messages and narratives to reduce SSB intake and encourage water intake and parent–child activities. To reach underserved youth and families, we identified Boys & Girls Clubs (B&GC) (youth-based community centers that serve an ethnically diverse and predominantly low socioeconomic status population) as a community partner and study setting. Participants (children ages 9–12 years and their parents) will be recruited from B&GC sites in Massachusetts, USA. Intervention efficacy will be assessed through a site-randomized trial (*N* = 2 youth-based community sites, pair-matched for size and racial/ethnic composition) with 54 parent–child pairs (*N* = 108) enrolled per site (*N* = 216 total). The comparison site will carry on with usual practice. Child and parental SSB and water consumption (primary outcomes) and parent and child beverage knowledge and attitudes (secondary outcomes) will be measured via self-report surveys. Additional outcomes include children’s anthropometric data, additional dietary behaviors, and physical activity. Measures will be collected at baseline, 2 and 6 months follow-up. With an estimated 20 % dropout rate, the study will have 80 % power to detect a group difference of 3.9 servings of SSBs per week.

**Discussion:**

Community-based approaches hold potential for decreasing SSB consumption among youth and families, particularly among underserved populations who are at greater obesity risk. This article describes the design and methods of a community-based behavioral intervention designed to reduce SSB consumption among youth and parents/caregivers.

**Trial registration:**

ClinicalTrials.gov NCT02890056. Date of Registration: August 31, 2016

## Background

Sugar-sweetened beverages (SSBs) are aggressively marketed to youth [1], comprise the leading source of added sugars to children’s diet [2], and provide little to no nutritional value [3–6]. Overall SSB intake has increased among U.S. youth over the past 10 years [7], averaging at 224 kcal/day (approximately 11 % of total caloric intake) [2]. Several studies have shown that high SSB intake is strongly linked with childhood obesity [2, 8–14]. Differences in children’s SSB intake parallel disparities in childhood obesity; higher rates of obesity and heavy SSB consumption (>500 kcals/day) are prevalent among low socioeconomic status (SES) children compared to high SES children, and among Latino and Black children compared to White children [8, 15, 16].

In contrast to excessive SSB consumption, research indicates that water intake among U.S. children and adolescents has been inadequate over the past decade [17, 18]. Data from the National Health and Nutrition Examination Survey (2009–2012) indicates that more than half (54.4 %) of youth ages 6–19 were not adequately hydrated (defined as urine osmolality ≥ 800 milliosmoles/kg), with nearly a quarter reporting consuming no plain water at all [18]. With over one third of U.S. children currently overweight or obese and at risk for numerous associated health risks, including having a shorter life expectancy than their parents [19], replacing SSBs with water is an important dietary behavior to target among children at elevated obesity risk.

As the majority of SSBs consumed by children take place at home [4, 8], approaches that address parental behaviors related to SSB and water intake (e.g., modeling, purchasing) are needed. Existing childhood obesity interventions that engage children and parents typically include children as passive recipients (e.g., receiving education from an expert) and utilize didactic approaches. These interventions have yielded modest effect estimates and lacked sustainability [20, 21]. Interventions that empower children as behavior change agents within their families have the potential to enhance child behavior change and parental engagement. The use of narrative-based approaches (presenting messages within the context of a story) may facilitate greater connection with target health messages compared to pure didactic instruction [22]. Examples of narrative-based approaches include integration of comic books, telenovelas, and live peer stories within interventions to reinforce targeted health behaviors. Narrative-based interventions have been associated with positive health behavior change among low SES, racial/ethnic minority adults [22–24].

To reach underserved youth and families, we identified local Boys & Girls Clubs (B&GC) of America as a community partner and intervention setting. B&GCs provide affordable after-school programs for ethnically diverse and predominantly lower socioeconomic status populations through nearly 4000 sites across the U.S. [25]. Central to the B&GC mission is partnering with families to promote healthy behaviors. If shown effective, the intervention will eventually be integrated into existing B&GC health programs delivered by trained B&GC staff. No community-based childhood obesity intervention to our knowledge has empowered children as change agents to convey key health behavior messages to parents. The purpose of this manuscript is to describe the design and methods of a community-based behavioral intervention to target SSB and water intake among an ethnically diverse sample of youth and families.

## Methods

### Study aim and design

This study aims to assess the feasibility and efficacy of a community-based behavioral intervention (delivered through B&GC sites) targeting SSB and water consumption among 108 parent–child pairs (*N* = 216) through a site-randomized trial. The site-level intervention will take place at two B&GC sites that were pair-matched for size and racial/ethnic composition. One site will be randomized to receive the intervention and the other site will receive usual care. The 6-week intervention consists of weekly group-based sessions with assessments conducted at baseline, 2 and 6 months follow-up (see Fig. 1 for study design). The primary outcomes are child and parental SSB and water intake, assessed via validated survey items. Secondary outcomes include child and parental knowledge and attitudes related to SSBs. Additional outcomes include children’s anthropometrics (height, weight and waist circumference), other dietary behaviors, and physical activity. We hypothesize that child participants in the intervention site will demonstrate reduced SSB intake and increased water intake compared to participants in the comparison site at 2 and 6 months follow-up. Study protocol and procedures were approved by the Boston University Medical Center Institutional Review Board.

**Fig. 1 Fig1:**
[figure not shown]
H_2_GO! Study Design

### Study setting and population

The B&GC of America is a national organization that provides affordable after-school programs for a large population (~4 million annually) of diverse youth (33 % White, 30 % Black, 23 % Latino) from predominantly low socioeconomic backgrounds through over 4000 club facilities across the U.S. [25]. Given the organization’s commitment to health promotion through health programs delivered by professionals trained in youth development, B&GCs serve as an ideal setting to deliver childhood obesity programs that target ethnically diverse and low SES populations. Given the wide local, state, and national reach of B&GCs to underserved youth, an efficacious behavioral intervention targeting SSB and water intake has high potential for sustainability and dissemination. Two B&GC sites (Worcester and Lowell) in Massachusetts, USA were selected for comparability in youth enrollment size and racial/ethnic composition and geographic spacing (>40 miles apart) to reduce contamination. See Table 1 for participating B&GC site characteristics.

**Table 1 Tab1:** Characteristics of Boys and Girls Club study sites (2012–2013) in Massachusetts, USA

	Worcester	Lowell
Total youth enrolled	1087	1619
Daily average school year attendance	180	211
% Hispanic	37	33
% Non-Hispanic White	16	20
% Non-Hispanic Black	16	19
% Multiracial	9	10

Parent–child pairs will be recruited from B&GC sites. *Child inclusion criteria* are: ages 9–12 years; current member at the B&GC study site; able to understand and communicate in English, able and willing to provide consent; parental/caregiver permission to participate; and no medical condition that limits ability to change beverage consumption behaviors. *Parental/caregiver inclusion criteria* are: parent/caregiver to a B&GC child member; 18 years or older; able to understand and communicate in English; able and willing to provide consent; and no medical condition that limits ability to change beverage consumption behaviors.

### Intervention condition

#### Development

The intervention was designed to address two behavioral targets: reducing the number of SSB servings consumed per day (recommended guideline of zero SSBs per day) and promoting water consumption (approximately 5–8 cups per day for youth participants and eight cups per day for parental participants). Intervention materials, strategies, format, and content were pilot-tested among a small sample (*N* = 12) of parent–child pairs at a B&GC study pilot site (Lawrence, MA) and finalized based on feedback from parent and child participants, B&GC staff, and observations from the research team. Informed by the Social Cognitive Theory [26] and the Social Ecological Model, the H_2_GO! Intervention was designed to target child and parent participants’ knowledge, attitudes (self-efficacy, outcome expectations, perceived social norms) and behavioral capabilities [27] related to SSB and water consumption.

### Intervention format, content, and strategies

The 6-week intervention consists of group-based weekly sessions (1-h sessions twice a week) delivered by trained B&GC program staff at the B&GC site. Each intervention session consists of a 1-h health module followed by a 1-h narrative module. Topics of the health modules include: understanding the benefits of water, sampling different types of fruit-flavored water, identifying SSBs, exploring the local grocery store, identifying barriers and facilitators to drinking water, and managing triggers for SSBs. See Table 2 for content and objectives targeted during each session. The narrative modules include intervention objectives and activities that reinforce knowledge, attitudes, skills, and behaviors targeted in the previous health component (e.g., if the health topic covers how to identify SSBs, the narrative module guides youth in creating their own messages and narratives through print, audio, or video materials that focus on how to identify SSBs).

**Table 2 Tab2:** H_2_GO! intervention content

Session	Health component	Narrative component
1	Topic: Water is Good for You! Objectives • Encourage youth to drink water during the session • Discuss benefits of drinking water • Discuss dehydration and over-hydration • Set individual water intake goals • Instruct youth how to keep track of water intake	Topic: Print Narratives to Promote Water Intake Objectives • Encourage youth to recall information learned about water in the previous health session • Guide youth in creating messages (tailored for their parents/caregivers) on drinking water through print narratives (e.g., PSAs, comics)
2	Topic: Re-think Your Drink Objectives • Help youth identify non-sweetened alternative beverages to SSBs • Conduct a group taste test of alternative beverage options • Encourage youth to try different beverage options • Discuss as a group experiences, reactions, and preferences from the taste test	Topic: Print Narratives to Encourage Sampling Different Types of Water Objectives • Encourage youth to recall information and experiences in the previous health session about the different types of water they tasted • Guide youth in creating messages (tailored for their parents/caregivers) on trying different types of water through print narratives (e.g., PSAs, comics)
3	Topic: Find the Facts Objectives • Instruct youth on nutrition labels • Guide youth on experiments with measuring serving size and sugar in a variety of SSBs • Help youth identify SSBs and non-SSBs	Topic: Print Narratives to Explain Beverage Nutrition Labels Objectives • Encourage youth to recall information about nutrition labels, serving sizes, and amount of sugar in SSBs in the previous health session • Guide youth in creating messages (tailored for their parents/caregivers) on reading nutrition labels, serving sizes, and amount of sugar in SSBs through print narratives (e.g., print PSAs, comics)
4	Topic: Explore the Corner Store Objectives • Identify different types of SSBs in a local corner or grocery store by reading labels • Distinguish between SSBs and non-SSBs in a convenience store by reading labels • Go into a store and not purchase SSBs	Topic: Audio Narratives to Explain Different Types of SSBs Objectives • Encourage youth to recall information about different types of SSBs discussed in the previous health session • Guide youth in creating messages (tailored for their parents/caregivers) on the different types of SSBs through audio narratives (e.g., short stories, word skits, raps, songs)
5	Topic: Water, water, everywhere Objectives • Identify opportunities to drink water in various settings • Explain ways to get water in various settings	Topic: Video Narratives to Overcome Barriers to Drinking Water Objectives • Encourage youth to recall information learned about barriers and facilitators to drinking water in the previous health session • Guide youth in creating messages for (tailored for their parents/caregivers) on overcoming barriers to drinking water through group-based video narratives (e.g., script development for skits; rehearsal for filming)
6	Topic: Triggers for SSBs Objectives • Identify triggers for SSBs • Brainstorm ways to avoid SSBs	Topic: Video Narratives to Overcome Barriers to Drinking Water and Manage SSB Triggers Objectives • Encourage youth to recall information learned in health sessions 5 and 6 • Guide youth in creating messages (tailored for their parents/caregivers) on managing SSBs triggers through group-based video narratives (e.g., revise skit scripts as needed; film group skits)
7	Topic: Boys and Girls Club Open House Objectives • Celebrate youth program completion through distribution of certificates and prizes • Strategically display print narratives throughout the club (e.g., by water fountains, vending machines) • Play video and audio narratives created through Club announcement system • Host a free taste test of flavored water for all Boys and Girls Club members	

Child participants will receive a reusable water bottle and a pictorial intervention booklet. Developed by the study principal investigator (PI) and research assistants, the brightly-colored 45-page booklet was culturally and linguistically-tailored to the study population and included intervention activity worksheets, parent–child take-home activities, fun facts and quizzes, and water and SSB consumption tracking sheets. Activity worksheets will be completed by participants during intervention sessions; and parent–child take-home activities will be completed following each session. Figure 2 presents sample intervention strategies utilized at the individual, interpersonal, and social and physical environmental levels, and Table 3 presents intervention strategies and activities used to target constructs of interest.

**Fig. 2 Fig2:**
[figure not shown]
Individual, interpersonal, and environmental-level intervention strategies

**Table 3 Tab3:** Strategies and constructs targeted by the H2GO! intervention

Intervention strategies and activities	Theoretical constructs targeted			
	Knowledge Related to Sugar-Sweetened Beverages (SSBs) and Water	Attitudes Related to SSB and Water Consumption (outcome expectations, self-efficacy)	Behavioral Capabilities and Skills Related to SSB and Water Consumption (self-monitoring, problem-solving, self-regulation skills)	Behaviors (reducing SSB consumption and promoting water consumption)
Individual level				
*Enactive mastery experiences* (blinded taste tests, local grocery store scavenger hunt of SSBs)	✓	✓	✓	✓
*Modeling* (B&GC staff and peer modeling of drinking water and choosing not to drink SSBs, self-monitoring and goal-setting demonstrations, youth development and sharing of narratives targeting key intervention messages)		✓	✓	✓
*Persuasive communication* (interactive demonstrations on hydration, sugar measurement demonstrations and experiments)	✓	✓		✓
*Active learning* (staff guidance, discussion of experiences, and provision of feedback on: 1) self-monitoring of SSB and water intake; 2) goal-setting on SSB and water intake; 3) problem-solving for barriers to drinking water; and 4) managing SSB triggers)	✓	✓	✓	✓
*Reinforcement* (point-based system to reward attendance and participation, points could be redeemed for prizes; staff provision of verbal encouragement for meeting behavioral targets)		✓		
*Didactic instruction* (instruction on how to read beverage nutrition labels, use of visual aids such as pictorial log sheets and pictorial activities, emphasis on one key message at a time)	✓			✓
Interpersonal level				
*Family support* (parent–child take-home activities, sharing of narratives targeting key intervention messages, parent attendance at Club Open House event)	✓	✓	✓	✓
*Peer modeling* (peer sharing of narrative narratives with guided discussions)		✓	✓	✓
*Group-based guided practice* (Boys and Girls Club staff supervision and provision of group feedback on water and SSB logs, group discussion, group games and activities)	✓	✓	✓	✓
Social and physical environmental level				
*Environmental restructuring* (onsite provision of drinking cups, water pitchers, and reusable water bottles during intervention sessions, display of print, audio, and narrative materials created throughout the Boys and Girls Club)		✓		✓
*Modeling* (Club Open House where youth shared their narratives and invited all Boys and Girls Club members to participate in taste tests)		✓		✓

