### Comparison condition

Participants in the comparison site will receive usual care at the B&GC (standard programming) during the study and complete assessments at baseline, 2 and 6 months follow up. The comparison B&GC site will receive an intervention toolkit including intervention materials, protocols, and supplies upon study completion.

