### Power calculation

Our sample size calculations are based on the primary hypothesis that child participants in the intervention site will have reduced SSB intake and increased water intake than child participants in the comparison site at 2 and 6 months follow-up. Results from our pilot data indicate that B&GC children consumed an average of 7.6 servings of SSBs over the past 7 days (SD = 6.5). Assuming that youth in the comparison site will experience no change in SSB intake from baseline to follow-up, a two-sided, two-sample t-test of means with alpha = 0.05 and 80 % power indicates that enrolling 45 children per group will allow us to detect a difference of 3.9 servings of SSBs per week, a clinically meaningful difference of approximately 550–940 kcals per week depending on serving size and SSB type. To account for 20 % dropout, we will enroll 54 parent–child pairs (*N* = 108) per site, yielding a total sample size of 216 participants.

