### Analysis plan for feasibility and efficacy outcomes

For feasibility outcomes, recruitment and retention rates will be compared across study sites and t-tests will be used to compare overall rates between the two sites. The number and reasons for failure to complete follow-up assessments will be reported. To analyze intervention engagement, youth session attendance rates for each session, percent of parent–child activities completed per week, number of narrative materials produced per child, and parent and child attendance rates at the club open house event will be reported. Intervention fidelity rates per session will be reported, and reasons for poor fidelity will be explored. For intervention acceptability and satisfaction, we will report descriptive statistics of intervention satisfaction ratings among children and parents and the proportions of children and parents who would recommend the intervention to others.

Distributions, descriptive statistics, and missing values will be examined for all efficacy study variables. Bivariate analyses will compare the characteristics of the intervention and comparison groups using two-tailed chi-square tests for categorical variables and two-tailed t-tests for continuous variables. These results will identify imbalances between groups that will be adjusted for in multivariable analyses. All analyses will utilize an intent-to-treat approach, with each child and parent participant enrolled in the intervention site analyzed as part of the group, regardless of intervention engagement. We will compare mean changes in our primary outcome (children’s SSB intake frequency) and secondary outcomes across intervention conditions using repeated measures mixed models. Generalized estimating equations will be used to account for clustering of observations within sites. Based on the relatively small sample size, complete case analysis with comparisons with baseline data will be used to address missing data as a result of loss to follow up.

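### The intervention works through groups, but the 80 % power assumes independent children and the only clustering level named, site, cannot absorb within-group correlation with one site per arm

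*Protocol article*

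**What the plan says.** **Delivery.** Intervention format, content, and strategies: "The 6-week intervention consists of group-based weekly sessions (1-h sessions twice a week) delivered by trained B&GC program staff". Table 2 has children script, rehearse and, in session 6, "film group skits". Table 3 adds "Boys and Girls Club staff supervision and provision of group feedback on water and SSB logs, group discussion, group games and activities" and marks this strategy as acting on SSB and water behaviour, the primary outcome domain.

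**Comparison.** Comparison condition: "Participants in the comparison site will receive usual care at the B&GC (standard programming) during the study". The study creates no groups there.

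**Allocation.** Study aim and design: "One site will be randomized to receive the intervention and the other site will receive usual care".

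**Sample size.** Power calculation: "a two-sided, two-sample t-test of means with alpha = 0.05 and 80 % power indicates that enrolling 45 children per group" can detect 3.9 servings per week, with SD 6.5. No ICC or design effect appears.

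**Analysis.** The analysis plan names repeated measures mixed models and then: "Generalized estimating equations will be used to account for clustering of observations within sites". No session group or staff leader is named as a level. The number of session groups, their size and whether membership is fixed are not stated anywhere.

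**The concern.** The article makes shared group process part of how the programme is meant to change drinking habits. Children in one group share a leader, peers and feedback on their logs, so their SSB changes may be positively correlated. The study creates this correlation on the intervention side only, which is a partially nested design. The sample size ignores it, and the one clustering level the analysis names coincides with the arm.

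At stake are the standard error of the intervention mean, the false-positive rate for child SSB and water intake, and the stated 80 % power. The source differs from ordinary differences between two clubs. If the site-level difficulty were handled by clustering on the child, for example, correlation within session groups would still be ignored. Unlike between-site variance, it can be estimated from the trial's own data, though imprecisely, when several groups run.

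**Working it through.** **1. Reproduce the plan's figure.** Inputs from Power calculation: difference 3.9, SD 6.5, two-sided alpha 0.05, power 80 %. The standardised difference is 3.9/6.5 = 0.6. The exact two-sample t-test needs 44.6, so 45 per group, with power 80.4 % at 45. The normal formula gives 44 per group and 81.2 % power at 45. The figure reproduces with a design effect of 1, so it contains no allowance for clustering.

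**2. Separate attrition first.** 54 enrolled per site with 20 % dropout leaves 54 × 0.80 = 43.2 per arm. At 43 per arm with independent children, power is 78.5 % (t-test), or about 79 %. This loss is not due to groups.

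**3. Add group correlation in the intervention arm only.** Group size m and ICC are assumptions; the article gives neither. SD 6.5 is taken to apply to the analysed outcome in both arms, with n = 45 analysed per arm.

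- Design effect: DE = 1 + (m − 1) × ICC
- Ratio of true to assumed SE of the difference: R = √((1 + DE)/2)
- Type I error when independence is assumed: 2 × (1 − Φ(1.96/R))
- Power with the correct SE: Φ(3.9/(6.5 × √(2/n) × R) − 1.96)

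Worked case, m = 12 and ICC 0.05: DE = 1 + 11 × 0.05 = 1.55; R = √(2.55/2) = 1.129; type I error = 8.3 %; 3.9/(6.5 × √(2/45)) = 2.846, and Φ(2.846/1.129 − 1.96) = 71.2 %.

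| m | ICC | DE | R | Type I error | Power |
|---|---|---|---|---|---|
| 9 | 0.01 | 1.08 | 1.020 | 5.5 % | 79.7 % |
| 9 | 0.05 | 1.40 | 1.095 | 7.4 % | 73.8 % |
| 9 | 0.10 | 1.80 | 1.183 | 9.8 % | 67.2 % |
| 12 | 0.01 | 1.11 | 1.027 | 5.6 % | 79.1 % |
| 12 | 0.05 | 1.55 | 1.129 | 8.3 % | 71.2 % |
| 12 | 0.10 | 2.10 | 1.245 | 11.5 % | 62.8 % |
| 15 | 0.01 | 1.14 | 1.034 | 5.8 % | 78.6 % |
| 15 | 0.05 | 1.70 | 1.162 | 9.2 % | 68.8 % |
| 15 | 0.10 | 2.40 | 1.304 | 13.3 % | 58.8 % |

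The reference for the power column is 81.2 %, the same normal formula with no clustering. The difference detectable with 80 % power rises from 3.84 to between 3.92 and 5.01 servings. With 43 per arm, attrition and grouping together give 77.9 % down to 56.9 %.

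**4. Can clustering by site absorb this?** In principle it would, because session groups are nested within the site. With one site per arm the robust variance rests on two clusters. In a model with an arm effect only, fitted by GEE under working independence, residuals sum to zero within each site. In simulated data with 45 children per site, the robust SE of the arm effect was zero to machine precision, against a model-based SE of 1.16 to 1.29. The named method therefore offers no protection.

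**5. The single-group case.** If all 45 children form one group, the formula gives power 73 % at ICC 0.01 and 50 % at ICC 0.05. The group is then the same unit as the site and the arm, so its variance cannot be estimated from the trial.

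**The case against.** The strongest objection is that a reader might infer that the intervention arm's error bars are too small as a matter of fact. The article does not support that. It never says more than one session group will run; if there is only one, the issue merges with the one-site-per-arm problem. At ICC 0.01 with groups of 9 to 15 the effect is close to negligible. This stands, and the point is conditional for that reason.

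Second, naming only the site is not in itself the fault, since site clustering would cover nested groups if there were enough sites. This also stands: the method fails because there is one site per arm.

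Third, a condensed article may leave random-effect terms to a fuller document. That is fair for the mixed model's detail. It does not cover the sample size, which is stated in full and assumes independence, or the clustering level, which is stated and unusable for this purpose.

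Fourth, comparison children also share staff and peers in standard programming, so treating them as clusters of one is a modelling assumption rather than a documented fact. Session groups and skit groups may also differ. Both caveats stand.

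Finally, a reader might infer that a group term would make the arm comparison valid. It would not: between-site variance stays inseparable from the intervention effect.

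**Conclusion.** The point holds conditionally. The article describes delivery through groups, gives a power figure that holds only for independent children, and names a clustering level that cannot account for within-group correlation here. If several session groups run and the ICC is positive, an analysis treating intervention children as independent understates the standard error, and 80 % power for 3.9 servings is optimistic.

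Over the assumed ranges the consequence goes from slight to material. Those ranges are illustrations, not estimates from the trial. The calculation uses normal quantiles, equal group sizes and SD 6.5 in both arms; small-sample degrees of freedom with few groups would lower power further. The attrition loss is separate and should not be attributed to grouping.

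**What to change.** - **Power.** State that the 80 % assumes independent children. Give it as a range over plausible session-group sizes and ICCs, with the attrition loss (about 79 % at 43 per arm before any clustering) shown on its own line.
- **Data.** Record each child's session group, and skit group if different, on the attendance record that club staff already keep under Feasibility outcomes. This should be done during delivery, because it may not be recoverable later.
- **Analysis.** If several groups run, add a session-group random effect for the intervention arm only, with comparison children as clusters of one and small-sample degrees of freedom. State the clusters-of-one choice as an assumption.
- **Single group.** If all children are taught together, state that this variance cannot be separated from site and arm and that the interval excludes it.
- **Limit.** State separately that none of this resolves the confounding of site with arm.

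The cost is one extra attendance column (two if skit groups differ), one model term and a restated power figure, with no extra participants. The downside is somewhat wider intervals and an imprecise variance component when groups are few.
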